#### **2.2.4 Risks of Pediatric Multivitamin Solution**

There have been rare reports of the following side effects associated with the pediatric multivitamin (MVI) solution that will be used as the placebo treatment: rash, erythema (redness of the skin), pruritis (itching), headache, dizziness, agitation, anxiety, diplopia (double vision), urticaria (hives), periorbital and digital edema (swelling around the eyes and swelling of the fingers). Multivitamin solution was used as the placebo for a prior placebo-controlled clinical trial of ceftriaxone in Lyme disease [138].

### **2.2.5 Potential Benefits**

If ceftriaxone is shown to have clinical efficacy with minimal to moderate risks, then the potential benefit from this study is large and outweighs the risks. Many measures will be in place to minimize risks of both the study drug and the mode of delivery. These include education of clinical trial staff, subjects and their caregivers on the potential risks of study drug and central venous access and how to minimize these risks, inclusion of experts in nephrology, infection disease and central venous catheters on the Steering Committee, and requirement for each site to have a nephrologist and infectious disease specialist available for consultation.

## **3. STUDY DESIGN**

### **3.1 Study Design Overview (Figure 5)**

Using a three-stage sequential, non-stop drug development design, we will determine optimal dosage, safety and efficacy of ceftriaxone in ALS. This design was chosen to expedite drug development while safely testing a new therapeutic agent in ALS. In STAGE 1, approximately 60 subjects will be randomized to one of three groups: ceftriaxone 2 grams daily, 2 grams twice daily or placebo. After seven days of treatment, they will be admitted to institutional GCRC or clinical research centers for a plasma and CSF pharmacokinetic study. All subjects will continue treatment after the STAGE 1 study and enter STAGE 2 to determine safety and tolerability after 20 weeks of daily treatment. If necessary, dosage adjustments may be made based on the analysis of data from the pharmacokinetic study during STAGE 1. After 60 subjects have completed at least 20 weeks of treatment, a decision will be made whether to continue to a phase III efficacy study (STAGE 3), and the single dosage to be used. An assessment will be made as to whether subjects can be given a safe dosage that will produce CSF levels reasonably expected to produce a biologic effect. If the decision is affirmative, the study will be expanded to a total of 600 randomized subjects at approximately 70 centers in US and Canada. Subjects in the STAGE 1 and 2 studies will continue on their assigned treatment arms until a decision on the STAGE 3 trial is made. They then will roll over into the larger phase (STAGE 3) study with subjects on active treatment in STAGE 1 and 2 being combined into the STAGE 3 portion of the study. New subjects will be randomized in a 2:1 fashion to receive treatment of ceftriaxone or placebo. Subjects will remain in study until 52 weeks after the last subject is randomized. The co-primary outcome measures for the phase III study will be survival free of tracheostomy or permanent assisted ventilation and the ALSFRS-R. Secondary outcome measures will include change in VC, evaluation of upper and lower extremity muscles using HHD, evaluation of quality of life, and the long-term safety and tolerability of ceftriaxone in this population.

The rationale for combining phase I-II-III for this study is that ceftriaxone is the most promising human drug from a large drug-screening program conducted by the NINDS. Since ceftriaxone is already an approved drug the only major phase I issue is its concentration in the CSF. The phase I-II-III study that we propose will speed the testing of this drug by at least two years as compared to separately funded and conducted phase I/II and III studies. Given that ALS is currently a uniformly fatal disease the rapid testing of such a promising agent is necessary. AIDS researchers came to a similar conclusion in 1990 in designing trials for AIDS [139].

Survival and ALSFRS-R were chosen as co-primary outcome measures. The two measures assess complementary and critical aspects of ALS progression. Survival remains the gold standard measure for an intervention whose goal is to modify disease progression. While several functional outcomes (including ALSFRS-R and pulmonary function) correlate with long term survival, they remain unproven surrogates for survival and for disease modification in general. Ceftriaxone has the potential to be a disease modifying treatment, and thus we believe it is appropriate to study sufficient numbers of patients for prolonged periods to provide a realistic chance to achieve a meaningful difference in survival. Survival is also the most robust of endpoints; it can be reliably determined in all subjects even if active participation in the study is terminated. As this study is designed as intent to treat, the uniform ability to obtain a survival outcome reduces the possibility of missing data.

Survival is not the only meaningful outcome for subjects with ALS, however. Functional measures have the potential to show meaningful differences with shorter study duration and fewer patients than what is needed to demonstrate a survival difference. The ALSFRS-R is a validated, reproducible, and reliable functional measure that assesses subject function across four domains: bulbar, fine motor, gross motor, and respiratory. It can be performed both in person and by telephone, and is highly correlated with survival. We have chosen ALSFRS-R as a co-primary outcome because it is a more sensitive measure of change in patient function than survival, and because meaningful differences can be detected in a shorter time period than is necessary to evaluate survival. The ideal outcome in this study is that significant differences between groups will be obtained for both primary outcome measures; however, a positive result on either measure would be clinically meaningful.

There are no data as yet available defining how sensitive any available marker is in predicting a specific survival effect. Some measures have been shown to correlate with survival, but the lack of a study with a clear survival effect during which these measures were obtained makes their relevance still a matter of conjecture. The pivotal studies demonstrating the efficacy of riluzole did not include any other outcome measures in current use. Studies employing functional markers may employ smaller sample sizes and still achieve reasonable power, but their utility is based on as yet untested assumptions about both the relation of such measures to survival and the effect that an effective treatment would be likely to have on these outcomes. We anticipate that by performing a study adequately powered for survival and ALSFRS-R and obtaining multiple secondary outcome measures as well, we will be able to validate these other measures for use in the future [140, 141]. This will be very important in facilitating future trials of different drugs and combinations that might be possible with smaller sample size.

## 3.2 Study Flow

**Figure 5: Study Flow**

[figure not shown]

## 3.3 Setting

The STAGE 1 and 2 studies will be conducted at up to 12 sites, selected because of their excellent record of recruitment, excellent compliance with study protocols and regulations, clinical research expertise and resources. The STAGE 3 study will be expanded to include approximately 70 sites in the United States and Canada.

Each site will employ a site investigator, an alternate physician-investigator who will be available at all times when the site PI is unavailable, a Research Nurse, Nurse Practitioner (NP) or Physician's Assistant (PA), or other qualified health professional, who will perform catheter training and catheter checks, a study coordinator and a clinical evaluator. A nephrology consultant, a gastroenterology consultant, a catheter specialist and an infectious disease specialist consultant will also be required at each site that will be available for clinical consultation for individual subjects.

## 4. SUBJECT SELECTION AND ENROLLMENT

### 4.1 Inclusion Criteria

1. Participants with familial or sporadic ALS diagnosed as laboratory supported probable, probable or definite according to the World Federation of Neurology El Escorial criteria [142], Appendix 2
2. Age 18 years or older
3. Capable of providing informed consent and complying with trial procedures.
4. Vital capacity (VC) at least 60% predicted value for gender, height and age at screening
5. Women must not be able to become pregnant (e.g. post menopausal, surgically sterile, or using adequate birth control methods) for the duration of the study. Adequate

- contraception includes: abstinence, hormonal contraception (oral contraception, implanted contraception, injected contraception or other hormonal (patch or contraceptive ring, for example) contraception), intrauterine device (IUD) in place for  $\geq 3$  months, barrier method in conjunction with spermicide, or another adequate method (as determined by steering committee member review). Women of childbearing potential must have a negative pregnancy test at screening and be non-lactating.
6. First ALS symptoms occurred no more than 3 years prior to screening visit
  7. Not taking riluzole, or on a stable dosage for at least thirty days prior to the screening visit
  8. Subject has a competent caregiver who can and will be responsible for administration of study drug. If there is no caregiver, another qualified individual must be available to administer the study drug.
  9. Geographic accessibility to the study site
  10. Subjects medically able to undergo placement of central venous catheter as determined by the investigator (to include absence of systemic infection, a medical disorder which precludes catheter placement)

#### **4.2 Exclusion Criteria**

1. Dependence on mechanical ventilation (invasive or non-invasive, including Continuous Positive Airway Pressure (CPAP) or Bilevel Positive Airway Pressure (BiPap) for any part of the day or night prior to the screening visit.
2. Exposure to ceftriaxone or any cephalosporin within 30 days prior to the screening visit.
3. History of known sensitivity or intolerability to ceftriaxone or to any other cephalosporin.
4. History of known sensitivity or intolerability to penicillin or any beta lactam (including mild rash).
5. Exposure to any other investigational agent within 30 days prior to screening visit.
6. Known immune compromising illness or therapy
7. Active gastrointestinal disease within 30 days of the screening visit
8. History of antibiotic-induced colitis
9. Active biliary disease, including gallstones
10. Presence of any of the following clinical conditions
  - a. Drug abuse or alcoholism
  - b. Unstable cardiac, pulmonary, renal, hepatic, endocrine, hematologic, or active infectious disease, including current malignancy
  - c. AIDS or AIDS-related complex
  - d. Unstable psychiatric illness defined as psychosis or untreated major depression within 90 days of the Screening Visit
11. Laboratory values: Screening alanine aminotransferase (ALT) greater than 3.0 times the upper limit of normal or, total bilirubin greater than 1.5 times the upper limit of normal, absolute neutrophil count of  $\leq$  or 1000/ul, platelet concentration of  $<100,000/\text{ul}$ , hematocrit level of  $<33$  for female or  $<35$  for male, or coagulation tests  $\geq 1.5$  times upper limit of normal.
12. Women of childbearing potential not practicing adequate contraception
13. History of known sensitivity to bile acids or ursodiol

***Riluzole.*** The use of riluzole will be permitted during the study. Subjects taking riluzole must be on a stable dosage for 30 days prior to screening. Subjects are not allowed to start taking riluzole during the trial. About 60 percent of patients with ALS in the United States are currently taking riluzole [95, 143]. Allowing subjects the choice of taking riluzole reduces dropout rate and ensures that the investigators know which subjects are taking riluzole.

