| Caregiver Burden Inventory                                    | X                      |                                 |                       |                  |   |   | X |   |    | X  |    |    |    | X  |    |    |    |
| Concomitant Medications                                       | X                      | X                               |                       | X                | X | X | X | X | X  | X  | X  | X  | X  | X  | X  | X  | X  |
| Adverse Events                                                |                        | X                               | X                     | X                | X | X | X | X | X  | X  | X  | X  | X  | X  | X  | X  | X  |
| Safety Labs (blood draw)                          | X                      |                                 |                       |                  | X | X | X | X | X  | X  | X  | X  | X  | X  | X  | X  | X  |
| Ceftriaxone Plasma Level (blood draw)                         |                        |                                 |                       |                  |   |   | X |   |    | X  |    |    |    | X  |    |    |    |
| Blood draw for Biomarkers                                     |                        |                                 |                       |                  |   |   |   |   |    |    |    | X  |    |    |    |    |    |
| Urinalysis/Spot Urine for protein and creatinine  | X                      |                                 |                       |                  | X | X | X | X | X  | X  | X  | X  | X  | X  | X  | X  | X  |
| Dispense Study Drug                                           |                        |                                 |                       | X                |   |   | X | X | X  | X  | X  | X  | X  | X  | X  | X  | X  |
| Drug Accountability/Compliance                                |                        |                                 |                       |                  |   |   | X | X | X  | X  | X  | X  | X  | X  | X  | X  | X  |
| Abdominal Ultrasound                                          | X                      |                                 |                       |                  |   |   | X | X | X  |    |    | X  |    |    | X  |    |    |

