### **6.2.1 Screening and Informed Consent**

At the screening visit, potential subjects will be informed about study procedures and will then sign an informed consent form (Appendix 3). Screening procedures will take place within 28 days of the baseline (randomization) visit. The inclusion/exclusion criteria will be reviewed and a medical history and full physical examination completed. The VC will be determined. Vital signs, weight and concomitant medications will be recorded. Safety laboratory tests will be performed including complete blood count (CBC) with differential, prothrombin time (PT), partial thromboplastin time (PTT), platelets, electrolytes (including phosphorous and calcium), BUN, creatinine, ALT, AST, total bilirubin, albumin, urinalysis including microanalysis (with culture and sensitivity when WBCs are present), and a pregnancy test for women of child-bearing potential. Pregnancy tests will be repeated as necessary throughout the trial.

An abdominal ultrasound will be performed at the screening visit to monitor for biliary disease. Hand held dynamometry for muscle strength will be performed, as well as the ALSFRS-R and Quality of Life questionnaires. The outcome measures performed at this visit will be the pre-treatment measures.

As part of the screening visit, the site investigator will determine the competence of caregiver to administer the study drug at home. Teaching will begin on the method of study drug administration and catheter care. All inclusion and exclusion criteria and safety laboratory tests will be reviewed by the site investigator prior to scheduling the catheter placement visit. If the subject passes all screening procedures and is confirmed as eligible, the catheter placement visit can be scheduled. The site study staff will electronically register the subject to the study and the subject will be assigned a screening identification number. Only registered subjects can go on to have catheter placement and randomization. This process will ensure that only subjects who are eligible for the study will proceed to have placement of a central venous catheter. A log will be kept at the site to record all subjects screened for entry into the study. This information will also be captured electronically. Demographic characteristics of all subjects who are screened will be recorded whether or not they qualify for entry into the study. The reason for non-qualification

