## **8. CRITERIA FOR INTERVENTION SUSPENSION, RECHALLENGE, OR PERMANENT DISCONTINUATION**

### **8.1 Intervention Suspension Related to Ceftriaxone Use**

**Study drug will be suspended under the following circumstances:**

(Please refer to the Manual of Operations for details regarding management of AEs)

- If the subject has *C. difficile* infection and is concurrently systemically ill with fever, leukocytosis or if the symptoms are refractory to treatment
- If the *C. difficile* infection results in pseudomembranous colitis
- If the subject is being treated for severe dehydration
- If the subject is symptomatic from biliary sludge
- If the subject is diagnosed with symptomatic cholelithiasis
- If the subject is diagnosed with invasive candidiasis
- If the subject is diagnosed with acute interstitial nephritis
- If the subject is diagnosed with acute tubular necrosis
- If the subject is diagnosed with renal failure
- If the serum creatinine doubles as compared to the screening visit value, the test will be repeated. If the value is confirmed (doubled as compared to screening visit value), study drug will be suspended while subject is evaluated.
- If the urinalysis is positive for Wright's or Hansel's stain as this is suggestive of eosinophiluria, or allergic interstitial nephritis
- If the spot urine protein is greater than 1000 mg. This is likely an indication of severe renal toxicity
- If the subject becomes oliguric, which is defined as urine output less than 500 mL/day. This can be an indication of severe renal toxicity
- If the Absolute Neutrophil Count (ANC) is less than 1.2 th/cmm

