**Subjects can not be rechallenged with study drug under the following circumstances:**

- If the subject is diagnosed with invasive candidiasis
- If the subject is diagnosed with AIN or ATN
- If the subject is diagnosed with renal failure
- If the spot urine protein is greater than 1000 mg

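### Spot urine protein is measured at screening but has no entry limit, although a value above 1000 mg on treatment permanently stops study drug

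*Combined protocol and SAP*

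**What the plan says.** **Entry (section 4.2).** Criterion 11 begins "Laboratory values: Screening alanine aminotransferase (ALT) greater than 3.0 times the upper limit of normal or, total bilirubin" and continues with limits for neutrophils, platelets, hematocrit and coagulation tests. It has no limit for urine protein or serum creatinine. The only renal exclusion is criterion 10b: "Unstable cardiac, pulmonary, renal, hepatic, endocrine, hematologic, or active infectious disease, including current malignancy". It gives no number.

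**Measurement (section 6.1).** The schedule row "Urinalysis/Spot Urine for protein and creatinine" is marked at screening, not at Day 0, and again at week 1 and every later visit.

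**Stopping (section 8.1).** Drug is suspended under this rule: "If the spot urine protein is greater than 1000 mg. This is likely an indication of severe renal toxicity". The list of findings that bar rechallenge repeats it: "If the spot urine protein is greater than 1000 mg". The serum creatinine rule in the suspension list works differently. It starts from a doubling of the screening value, calls for a repeat test, and then says: "If the value is confirmed (doubled as compared to screening visit value), study drug will be suspended while subject is evaluated".

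**Review before the catheter (section 6.2.1).** "All inclusion and exclusion criteria and safety laboratory tests will be reviewed by the site investigator prior to scheduling the catheter placement visit". The screening laboratory list in that section includes "urinalysis including microanalysis (with culture and sensitivity when WBCs are present), and a pregnancy test for women of child-bearing potential". It attaches no urine protein limit.

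**The concern.** The entry and stopping rules use the same measurement but do not meet. The stopping limit is absolute. It refers neither to the subject's own screening value nor to a confirming repeat, and because rechallenge is barred it amounts to permanent discontinuation. A subject who enters above the limit cannot satisfy the rule at the first urine sample on treatment unless the level falls.

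At stake is an avoidable invasive procedure. Such a subject would undergo tunneled catheter placement for about one week of blinded study drug, in either arm, when a result already obtained at screening could have prevented it. A long-standing proteinuria might also be recorded as a sign of drug toxicity, because section 8.1 describes the value in those terms.

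**Working it through.** The plan gives no figure to reproduce for this point. The main check sets the rules side by side, followed by a short calculation of risk per subject.

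**Rule check.** Take a subject with spot urine protein stably above 1000 mg, all criterion 11 values acceptable, and renal disease not considered unstable.

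1. *Screening.* The value is obtained (section 6.1). No criterion in section 4.1 or 4.2 names it, so no explicit exclusion is met.
2. *Review before the catheter.* The investigator checks criteria and safety laboratory tests (section 6.2.1), and criteria are checked again at placement (section 6.2.2). Neither step carries a protein limit. The subject may be declined by judgment but does not have to be.
3. *Catheter, randomization, first dose.* All are permitted.
4. *Week 1.* The next scheduled urine is taken. If the level persists, it exceeds 1000 mg and drug is suspended (section 8.1, suspension list).
5. *After suspension.* The same finding bars rechallenge (section 8.1), so the stop is permanent.

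**Contrast with the neighboring creatinine rule.**

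| | Serum creatinine | Spot urine protein |
|---|---|---|
| Compared with screening value | Yes (doubling) | No (above 1000 mg) |
| Repeat before the rule takes effect | Yes | No |
| Listed as barring rechallenge | No | Yes |

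The creatinine rule needs no entry limit to be consistent, because it adjusts to where the subject began. The protein rule does need one.

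**Risk per affected subject.**

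- *Arterial puncture.* Section 2.2.3 gives 1% to 8.4%, with the lower end possibly linked to the jugular route that this trial uses. Section 7.3 states 8.4% for radiologically placed catheters. The range to carry is 1% to 8.4%.
- *Bloodstream infection.* Sections 2.2.3 and 7.3 give 0.34 per 1000 catheter days in home care. For a catheter placed on Day 0 and in place until week 1: 0.34 / 1000 × 7 = 0.00238, or about 0.24%. The figure grows in proportion to days if the catheter is placed before Day 0 or stays in after drug stops. Section 2.2.3 also notes a higher likelihood of infection at the jugular site, which this rate does not separate out.

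**Number of subjects.** The documents give no frequency of proteinuria at this level in the screened population, so no expected count is calculated.

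**The case against.** The strongest reply is that clinical judgment already covers the case. Criterion 10b excludes unstable renal disease. Inclusion criterion 10 asks the investigator to confirm fitness for the catheter. The criteria are reviewed before the catheter is scheduled and again at placement, and section 3.3 requires a nephrology consultant at each site. For harm to occur, an investigator would have to see a value that section 8.1 links to severe renal toxicity and go ahead anyway. Much of this stands: many such subjects would probably be declined. But these are discretionary steps at about 70 sites, and none carries a protein limit. The repeat testing allowed in section 6.2.1 is for suspected error and does not help when the value is true and stable.

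A second reply is that entry criteria need not mirror every stopping rule, and that section 8.1 is aimed at drug toxicity, which an unchanged pre-treatment value does not show. That is fair as to intent. The wording is nevertheless mandatory and makes no exception for a known baseline. The Manual of Operations, which is not among the documents, may add management detail, but section 4.3.3 ties eligibility to the inclusion and exclusion criteria.

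Three stronger readings are tempting, and the documents do not support them.

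- *The protocol contradicts its own catheter safeguards.* It does not. Section 6.2.1 promises that only eligible subjects get a catheter, and this subject is eligible as written. Section 5.1.2 aims to avoid a catheter in someone who cannot start drug, and this subject does start.
- *The reviewing investigator would not see the value.* The section 6.2.1 list does not name spot protein, but it is not worded as exhaustive, and the schedule puts spot protein on the same row as urinalysis.
- *A limit of 1000 mg without a denominator makes the rule unworkable.* Creatinine is collected with the protein, which suggests a ratio, and the manual may state the unit. This is a clarification only.

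**Conclusion.** The mismatch is real and the point is minor. As written, a subject with stable spot urine protein above 1000 mg is formally eligible for a tunneled catheter and must permanently stop study drug at about week 1, unless an investigator declines the subject by judgment.

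The conclusion rests on reading the two section 8.1 lists together and on the level persisting from screening to week 1. The number of subjects affected is unknown and may be near zero. For any one of them, the avoidable risk is the 1% to 8.4% chance of arterial puncture and roughly 0.24% of bloodstream infection for each 7 catheter days.

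A reader might infer that early forced stops would weaken the efficacy comparison. Nothing in the documents points to enough such subjects to matter, and all subjects stay in the intention-to-treat analysis. The issue is patient safety, not the trial's answer.

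**What to change.** Two short text changes by amendment:

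1. **Section 4.2, criterion 11.** Add an exclusion for screening spot urine protein above the section 8.1 limit, in the same unit as section 8.1. As a clarification, state that unit in both places, since a spot sample needs a denominator.
2. **Section 8.1.** Hold study drug at the first value above the limit, obtain a prompt repeat, and make the stop permanent only if the repeat confirms it. The creatinine rule already calls for a repeat. Holding drug while waiting keeps the renal protection intact.

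No new scheduled test or visit is needed, because spot protein and creatinine are already collected at screening. The cost is a few more screen failures and an occasional repeat urine.

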will be recorded for all subjects who are not eligible. The reason for non-participation will also be recorded for subjects who are eligible but choose not to participate in the trial. If a subject fails screening for the study, the subject can be re-screened if the Site Investigator determines it is appropriate to do so. At any time during the study, repeat laboratory tests can be obtained if the Site Investigator or central laboratory thinks that a laboratory test result is in error. Additional laboratory tests, including coagulation tests, may also be obtained at any time during the study, at the discretion of the Site Investigator.

Between screening and the catheter placement visit, the subject and caregiver may return to the site for teaching visits. At these visits, the study Nurse, Physician Assistant or Physician will teach use and care of central venous catheters. The caregiver will need to pass a competency test prior to catheter placement. As many visits for training as are needed will be permitted.

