### **6.2.2 On-Study Evaluations**

**Central Venous Catheter Placement Visit.** The catheter for venous access will be placed within 26 days of the screening visit. The entry criteria will be reviewed again and the subjects will have vital signs checked. A single-lumen tunneled Hickman catheter will be placed in the outpatient setting by a trained operator in the Interventional Radiology lab or other appropriate setting within the institution. Placement will follow institutional guidelines at each site, which may include placement under fluoroscopy and/or the administration of an antibiotic as part of the procedure. Prior to study initiation, all sites will provide written verification of experience with percutaneous catheter placements. Full details of catheter implantation and subsequent use and care will be provided to the sites in the Manual of Operations. Each subject will have a radiographic evaluation (such as x-rays or fluoroscopy) following catheter placement to assess for pneumothorax and for evaluation of placement of the tip of catheter.

If possible, the baseline (day 0) visit and randomization will occur on the same day as the catheter placement. At this time, the study drug will be dispensed and the first dose will be administered. Due to differences in site organization, some subjects may not be able to be randomized and provided with study drug at the catheter placement visit. These subjects will be randomized and receive their study drug (Baseline visit, day 0) no more than 28 days after the screening visit. These subjects will flush the catheter daily with normal saline until randomization occurs. Every effort should be made to randomize and have subjects begin study drug as soon as possible following catheter placement.

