## **Leukopenia, Thrombocytopenia, and Prolonged Prothrombin Time**

Leukopenia can occur with ceftriaxone use [103]. Complete blood counts will be monitored during study drug treatment. If the neutrophil count falls below 1200, the study drug will be held. Re-initiation of the study drug will be considered in consultation with the site infectious disease consultant.

Thrombocytopenia and Prolonged Prothrombin Time (PT) are rarely reported (less than 1%) side effects that may lead to bleeding (hemorrhage).

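### Exclusion criterion 11 sets the neutrophil entry limit at about 1000/ul, below the 1200/ul suspension limit, so an unchanged count of 1001-1199/ul can pass entry and then trigger a hold at week 1

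*Combined protocol and SAP*

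**What the plan says.** **Entry.** Section 4.2, criterion 11, lists the laboratory exclusions, and the neutrophil limit appears in the run "or 1000/ul, platelet concentration of". The operator before the number is unclear in the available copy, possibly because of the PDF conversion.

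**On treatment.** Section 8.1 lists the circumstances in which drug will be suspended. One is "If the Absolute Neutrophil Count (ANC) is less than 1.2 th/cmm". Section 7.1, under leukopenia, gives the same figure in different words: "If the neutrophil count falls below 1200, the study drug will be held". By contrast, the creatinine item in the Section 8.1 list is tied to the subject's own baseline and must be confirmed: "If the serum creatinine doubles as compared to the screening visit value, the test will be repeated".

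**Checks before dosing.** Section 6.2.1 says "All inclusion and exclusion criteria and safety laboratory tests will be reviewed by the site investigator prior to scheduling the catheter placement visit", sets the window with "Screening procedures will take place within 28 days of the baseline (randomization) visit", and leaves extra testing open: "Additional laboratory tests, including coagulation tests, may also be obtained at any time during the study, at the discretion of the Site Investigator". At the catheter visit, Section 6.2.2 says "The entry criteria will be reviewed again and the subjects will have vital signs checked". At baseline, the stated bars to randomization are fever and significant catheter complications.

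**After a hold.** Section 7.1 allows restarting to be considered with the site's infectious disease consultant. Section 8.1 lists rechallenge once the ANC is back within the normal range.

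**The concern.** When one laboratory test governs both entry and suspension, the entry limit should not be the looser of the two. Otherwise a subject can satisfy one rule and break the other with the same value.

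What is at stake is patient burden. Drug delivery requires a tunneled catheter, placed before the first dose. The protocol takes care elsewhere to avoid futile catheters: Section 5.1.2 puts training and competency testing ahead of placement so that nobody has a catheter and then cannot begin treatment, and Section 6.2.1 uses registration to keep ineligible subjects from reaching placement. A neutrophil limit below the suspension limit leaves a small gap in that protection. The hold is not specific to an arm, so it would apply to placebo subjects as well.

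**Working it through.** The plan gives no figure to reproduce here. The check is a unit conversion and a comparison of rules.

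1. **Common units.** 1.2 th/cmm = 1.2 x 1000 cells per cubic millimetre = 1200/ul, which matches the 1200 in Section 7.1.

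2. **Overlap.** Eligible: ANC above 1000/ul. Suspended: ANC below 1200/ul. Both hold for 1001-1199/ul in whole counts. The distance between the limits is 1200 - 1000 = 200/ul. Reading the unclear operator as strictly below 1000 would add only the value 1000 itself.

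3. **Could another check close the gap?**

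| Step | Requirement | Sets a 1200/ul floor? |
|---|---|---|
| Screening (6.2.1) | Criteria and safety labs reviewed by the investigator | No; the criterion is about 1000/ul |
| Exclusions 6 and 10b (4.2) | Immune compromise; unstable hematologic disease | Not clearly, for a stable mild low count |
| Inclusion 10 (4.1) | Medically able to have a catheter, in the investigator's view | No |
| Catheter visit (6.2.2) | Entry criteria reviewed again; vital signs | No |
| Baseline (6.2.2) | No fever or significant catheter complication | No |
| Extra tests (6.2.1) | At the investigator's discretion | No |

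4. **Next scheduled count.** The schedule in Section 6.1 and the visit text in Section 6.2.2 place safety labs at screening and then at weeks 1, 2 and 4, with none at catheter placement or baseline. With screening up to 28 days before baseline, the interval can reach 28 + 7 = 35 days, or 38 with the +3 day visit window. This matters for drift, not for an unchanged count.

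5. **Exposure before the week 1 count (Stage 3).** One dose is given on Day 0, then two per day. If none is missed and blood is drawn before that morning's dose, Day 7 gives 1 + 2 x 6 = 13 doses. The visit window runs from Day 4 (1 + 2 x 3 = 7) to Day 10 (1 + 2 x 9 = 19). The pre-dose draw is an assumption: the morning pre-dose instruction in Section 6.2.2 concerns ceftriaxone levels, which are not scheduled at week 1 in Stage 3.

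6. **Number affected.** The documents give no frequency for counts of 1001-1199/ul. For scale only, an assumed 0.1% to 1% of the 540 additional Stage 3 subjects would be 540 x 0.001 = 0.54 to 540 x 0.01 = 5.4 subjects. That range is not evidence of the true number.

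7. **After the change.** If eligibility requires at least 1200/ul and suspension applies below 1200/ul, no value satisfies both rules.

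**The case against.** **The rule may be meant for a drug effect.** Section 7.1 speaks of a count that falls, and Section 8.1 is headed as suspension related to ceftriaxone. An unchanged pre-treatment count is not obviously a toxicity signal. This has some force and lowers confidence. But the Section 8.1 item is unqualified, and the neighbouring creatinine item shows that the authors wrote a baseline comparison where they wanted one.

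**Discretion and the Manual of Operations.** An investigator who knows the 1200 rule sees the screening labs before scheduling the catheter and can defer or retest. Section 8.1 refers to the Manual of Operations for adverse event management, and that manual is not among the documents. Both points stand, but neither supplies an entry floor in the protocol.

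**The fix is partial.** A subject screened just above 1200/ul can fluctuate below it and reach the same outcome. That is true. The change removes only the formal contradiction.

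**Stronger readings to avoid.** A reader might infer that the catheter is wasted or treatment lost. The documents do not show that: Section 7.1 allows restarting to be considered, and a low ANC is absent from the Section 8.1 list of conditions barring rechallenge. Section 8.1 does tie rechallenge to a return to the normal range, which could prolong the hold, but the laboratory's range is not given. A reader might also infer unmonitored neutropenia. Counts are scheduled at weeks 1, 2 and 4, and Section 2.2.2 reports that neutropenia reversed on stopping drug.

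**Conclusion.** The inconsistency is real on the text. A Stage 3 subject with a stable ANC of 1001-1199/ul can be eligible, have a tunneled catheter placed, start drug, and meet the literal suspension rule at week 1 with an unchanged value. The limits differ by 200/ul.

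The conclusion rests on reading the Section 8.1 item as written, on a count that stays within that band, and on no unscheduled test or investigator decision intervening first. The length of the hold is undetermined, and the number of subjects is unknown and probably very small. There is no effect on power or on the survival and ALSFRS-R tests. Severity is minor and confidence moderate.

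**What to change.** In Section 4.2, criterion 11, exclude a screening ANC below 1200/ul, or a higher value set by the study's safety experts, and write the operator unambiguously in the same edit. The entry limit is then no longer below the suspension limit.

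This is a one-line change with no new visit or test. It costs a few candidates with screening counts of 1001-1199/ul, and it does not prevent later drift below 1200/ul from a count just above it. A repeat test or a comparison with the screening value, on the model of the creatinine rule in Section 8.1, is an alternative, but it would change an on-treatment safety rule. Amending the entry limit leaves that rule as it is.
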